### Pre-existing disease condition

A pre-existing disease condition refers to a disease state that was present at the time of the screening visit for this study. This disease state should be recorded in the general medical history and baseline physical condition CRF.

During the study, an adverse event (AE) should only be recorded if the frequency, severity, or nature of a pre-existing medical condition worsens. When recording such events on the AE page of the CRF, care should be taken to use appropriate descriptions to convey the concept that an existing medical condition has changed (e.g., 'more frequent headaches').

### Adverse events related to drug overdose or administration errors

Drug overdose refers to the unintentional or intentional administration of a dose higher than the level currently being studied. Neither drug overdose nor incorrect administration of the investigational drug itself should be considered an AE, but they may lead to AEs. AEs related to drug overdose or incorrect administration of the investigational drug will be classified as SAEs, recorded on the AE page of the CRF, and reported immediately (i.e., within 24 hours of becoming aware of the event).

# Data Collection and Management

## Data Confidentiality

Information regarding research subjects will be kept confidential and managed in accordance with applicable laws and regulations.

## Central Monitoring

Before the study begins, at the central initiation meeting, the investigator and their team review the protocol, informed consent form, and CRF, among other documents. During the study, monitors will regularly visit the center to verify records and reports of SAEs, the existence of informed consent forms, compliance with inclusion/exclusion criteria, the completeness of patient records, the accuracy of CRF entries, adherence to the protocol and Good Clinical Practice guidelines, as well as the progress of patient recruitment, ensuring that the investigational drug is stored, distributed, and accounted for according to regulations. During these visits, key research personnel must be present to assist the monitors.

## Data Collection

This trial uses Case Report Forms (CRF) to collect data in clinical research, and designated researchers will enter the data into the CRF according to the protocol requirements. Researchers must retain the source documents for each subject, including original medical records and all other paper data or records. The data entered into the CRF must be traceable to the source documents in the subject files. The principal investigator is responsible for ensuring that the data entered into the CRF is complete, accurate, and updated in a timely manner.

Radiological and imaging data will be obtained by the center and interpreted at the center.

## Database Management and Quality Control

Data Entry: During the data entry process, the investigator or authorized research personnel may contact the data department at any time to communicate and resolve any questions encountered.

Data verification: The methods of data verification during the data management process include logical data verification, manual verification, medical verification, and statistical pre-analysis verification stages. Data inquiries will be generated for discrepancies and missing values, and the designated research center staff must respond to the inquiries immediately and make necessary modifications to the data. If the responses meet the requirements, the inquiry will be closed. If the data queries remain unresolved or if new queries arise after updating the database based on the previous data query responses, the researcher or their authorized personnel must provide new answers. The above process will be repeated until all data in the database is confirmed to be accurate.

The terminology from the International Medical Dictionary (MedDRA) will be used to code medical history/current medical conditions and adverse events.

## Database Lock

At the end of the study, it will be determined whether any protocol deviations occurred. After completing the above steps and confirming that the data is complete and accurate, the database will be locked, clearly defining the data available for analysis. Before the database lock, the project manager will convene a data review meeting with the principal investigator, statistician, and data manager to determine the analysis population. After the lock, the DM will submit the locked data to the statistician for statistical analysis.

The data can be locked once the following conditions are met:

- All data has been collected and entered into the database.
- All coding has been verified and confirmed.
- All data queries have been resolved (including those raised during data review).
- Database QC has passed.
- Data review has been completed.
- Verification of original documents has been completed.
- The verification of SAEs has been completed.
- All investigators' signatures have been obtained.
- The analyzable cases have been defined and saved in the final analysis database.
- The statistical analysis plan has been signed.

Prior to any database modifications on the locked data, joint written approval from the biostatistics and data management director and the clinical research director is required.

# Statistical analysis

The statistical analysis plan will be developed after the protocol is finalized and will be finalized before database lock. The statistical analysis plan will specify and describe in detail all statistical analyses to be conducted based on the main features of the protocol. All statistical analyses will be computed using SAS statistical analysis software.

This study provides statistical descriptions of all variables obtained at each observation time point, unless the protocol specifies that statistical descriptions are not required at specific time points. The results of this study primarily utilize descriptive statistical analysis. For continuous variables, standard descriptive statistical results include mean, standard deviation, median, maximum, minimum, while count data and ordinal data list frequencies (proportions), rates, and 95% confidence intervals (CI). The number of subjects enrolled, as well as dropout and exclusion cases, are described. The final analysis of the study will be based on data collected from subjects throughout the study period. Statistical methods will be detailed in the statistical analysis plan.

## Data Analysis Set

All observational indicators of the subjects are included in the statistical analysis. The dataset includes the Full Analysis Set (FAS), Safety Set (SS), and Per Protocol Set (PPS). Efficacy analysis will utilize both FAS and PPS, with FAS as the primary analysis set. Safety analysis will use SS.

**FAS:** Refers to the collection of all cases that have used the investigational drug at least once according to the protocol, excluding cases that have been removed; Cases that did not experience tumor progression during the observation and follow-up periods will have their tumor progression time treated as censored, with the censoring time being the most recent confirmation of no tumor progression.

**SS:** Refers to the population of subjects who have signed informed consent and have used the investigational drug at least once.

**PPS:** A subset of the FAS population, referring to all cases that have used the investigational drug according to the protocol for at least 2 weeks and meet the inclusion criteria for the FAS. Cases that have taken the drug for less than 2 weeks but have experienced radiologically confirmed disease progression within 12 weeks after starting the drug, and meet the inclusion criteria for the FAS, will also be included in the PPS. Cases in which tumor progression was not observed during the observation and follow-up periods will have their tumor progression time treated as censored, with the censoring time being the most recent confirmation of tumor non-progression.

Cases that are excluded should be retained for reference; except for cases that have previously used the drug being classified as SS, other cases (those that have not used the drug at all) will not be included in the statistical analysis.

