# Research design

## Overview of the research design

This study is a single-center, open-label, single-arm, exploratory study, planning to enroll 30 cases of unresectable advanced hepatocellular carcinoma patients (see sections 4.1 and 4.2 for details).

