## Sample size calculation basis

This study is an exploratory study, using a fixed sample size of 30 cases.

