## Exclusion Criteria

Before statistical analysis of the data, the principal investigator and the statistical unit will determine whether individual cases should be excluded. In the event of any of the following situations, the principal investigator should comprehensively assess whether to exclude the subject based on the extent of the subject's completion of the study and the reasons for early withdrawal, and provide relevant explanations. The CRF form should be retained for reference.

1. The subject violated important inclusion/exclusion criteria;
2. During the study period, the subject did not comply with the study protocol, such as not using the investigational drug, being unable to collect safety evaluation samples as required by the study protocol, or having no data at all;
3. During the study period, the investigator believes that the subject has other factors that prevent continued participation in the study, such as the concurrent use of other antitumor therapies during the study period, and actually terminates the subject's participation in the study.

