### Objective response rate (objective response rate, ORR)

The objective response rate is defined as the proportion of subjects with the best overall response confirmed as CR or PR (using both RECIST v1.1 and mRECIST criteria for tumor assessment, with RECIST v1.1 as the primary criterion). In calculating ORR, any partial or complete responses confirmed prior to any other antitumor therapy are counted as responses, regardless of how many assessments were missed prior to the response. When the best overall response of subjects is 'unknown' or 'not assessed', it is considered as non-response when estimating ORR.

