## Efficacy analysis

### primary efficacy endpoints

Summarize the ORR, including the number of subjects with ORR, the percentage, and the 95% confidence interval (calculated using the Clopper-Pearson method).

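### The primary efficacy set (FAS) allows treated patients to be removed on post-treatment grounds by people not stated to be blind to response, which can bias the ORR, probably upward

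*Protocol*

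**What the plan says.** Section 10.1 (Data Analysis Set) analyses efficacy in the FAS and the PPS, with the FAS primary. The FAS consists of cases that "used the investigational drug at least once according to the protocol, excluding cases that have been removed". The section closes by saying what happens to excluded cases: they are left out of the statistical analysis, "except for cases that have previously used the drug being classified as SS". So a patient can be treated, removed, and then counted for safety only.

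The removal rule is in Section 4.4, the second of two sections headed Exclusion Criteria. The principal investigator and the statistical unit decide on individual cases before the analysis. When a listed ground applies, "the principal investigator should comprehensively assess whether to exclude the subject based on the extent of the subject's completion of the study", together with the reasons for early withdrawal. The grounds are:

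- violation of important eligibility criteria, with the term important left undefined;
- failure to follow the protocol, with examples that include having no data;
- factors that end participation, with concurrent use of other antitumor therapy as the example.

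Under Section 9.5 (Database Lock), the project manager "will convene a data review meeting with the principal investigator, statistician, and data manager to determine the analysis population" before lock.

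Section 7.4.4 gives the rule for missing responses: "When the best overall response of subjects is 'unknown' or 'not assessed', it is considered as non-response when estimating ORR".

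Section 3.1 describes a "single-center, open-label, single-arm, exploratory study", and Section 9.3 has the images both obtained and interpreted at the centre.

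**The concern.** A full analysis set is meant to fix the denominator by facts known at or near the start of treatment. Here it depends on decisions taken at the end, from information that arises after treatment starts: how long the patient stayed, why the patient left, compliance, missing data, other therapy. Such facts are related to response. By the time the decisions are made, the responses have been read at the same centre and there is no treatment blind. Nothing in the protocol limits removal to baseline facts or asks for the decision to be made without knowledge of response.

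The ORR and its interval are the trial's one primary result, and with 30 patients a few discretionary removals move both. The same set serves DCR, PFS and TTP, so those populations would be selected in the same way.

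The missing-response rule in Section 7.4.4 works only for patients still in the set. A treated patient with no usable scan counts as a non-responder if kept, and disappears from numerator and denominator if removed. Section 4.4 makes that choice discretionary.

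**Working it through.** **Inputs from the protocol.** N = 30 (Section 3.2: "using a fixed sample size of 30 cases"). The primary endpoint is the ORR with a two-sided "95% confidence interval (calculated using the Clopper-Pearson method") (Section 10.3.1). No null rate, target rate, alpha, power or precision is stated, so the figure of 30 cannot be re-derived.

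**Assumptions.** The protocol gives neither a responder count nor a number removed. I take 9, 12, 15 or 18 responders among 30 treated patients, and 3 or 6 removals (10% or 20%). The denominator of 30 ignores any replacement of lead-in subjects.

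**Interval formula.** For x responders among n, the lower limit is the 2.5% point of Beta(x, n − x + 1) and the upper limit is the 97.5% point of Beta(x + 1, n − x).

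**Check of the method** on the donafenib study ZGDH1B cited in Section 1.3.2.2. The denominators 51 and 53 are inferred from its percentages.

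- 4/51 = 7.8%, computed limits 2.2% to 18.9%; the protocol prints 2.0% to 19.0%.
- 3/53 = 5.7%, computed limits 1.2% to 15.7%; the protocol prints 1.0% to 16.0%.

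Both agree once limits are rounded to whole percents.

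**Shift when k non-responders are removed.** x/(30 − k) − x/30 = xk / [30(30 − k)]. For x = 15 and k = 3 this is 45/810 = 5.6 points; for k = 6 it is 90/720 = 12.5 points.

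| Responders | None removed (n = 30) | 3 non-responders removed (n = 27) | 6 non-responders removed (n = 24) |
|---|---|---|---|
| 9 | 30.0% (14.7 to 49.4) | 33.3% (16.5 to 54.0) | 37.5% (18.8 to 59.4) |
| 12 | 40.0% (22.7 to 59.4) | 44.4% (25.5 to 64.7) | 50.0% (29.1 to 70.9) |
| 15 | 50.0% (31.3 to 68.7) | 55.6% (35.3 to 74.5) | 62.5% (40.6 to 81.2) |
| 18 | 60.0% (40.6 to 77.3) | 66.7% (46.0 to 83.5) | 75.0% (53.3 to 90.2) |

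**Dependence on who is removed.** With 15 responders and 3 removals, of whom r are responders, the ORR is (15 − r)/27: 55.6% for r = 0, 51.9% for r = 1, 48.1% for r = 2 and 44.4% for r = 3. If removal is unrelated to response, the expected ORR is unchanged.

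**Effect on the interval.** Let the number of responders be Binomial(30, 0.5) and drop k non-responders. The probability that the lower 95% limit lies above the true 50% is 2.1% for k = 0, 4.9% for k = 3 and 18.1% for k = 6, against a nominal maximum of 2.5%.

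**The case against.** Several points on the other side are sound.

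*Direction.* A reader might infer that the rule necessarily inflates the ORR. The protocol does not support that, because nothing confines removal to non-responders. The third ground speaks of concurrent antitumor therapy, and Section 5.6 lists surgery among the barred treatments. In the triplet study cited in Section 1.5, 8 of 36 patients were downstaged to resectable disease; 4 had curative resection and 1 a transplant. Such patients are plausibly responders, and removing them would lower the ORR. Progression is not itself a removal ground: Section 4.3.2 treats it as a reason to stop treatment, and Section 4.3.3 sends those patients to survival follow-up. What stands is that the bias can go either way. Upward is the likelier direction, because early leaving, non-compliance and absent data mostly mark patients without a response.

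*Who decides.* A reader might infer that the principal investigator decides alone. Section 4.4 shares the decision with the statistical unit, and Section 9.5 brings the statistician and data manager into the meeting. Explanations are required and exclusions are to be described. This limits abuse and helps a reader judge the result. It does not supply blinding, and holding the meeting before lock does not hide open-label responses.

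*Section 7.4.4.* A reader might call this a contradiction. The two rules can be applied together: one scores patients within the set, the other defines the set. The second weakens the first where they overlap, and no more than that.

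*Stakes.* The study is exploratory and mainly descriptive, and no decision threshold hangs on the ORR. That lowers the consequence of a biased estimate, but the ORR and its interval remain the primary output.

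*The SAP.* It could specify more, but the protocol itself fixes this FAS definition. A SAP could repair it only by departing from the protocol.

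**Conclusion.** The concern holds as a defect in the definition of the primary analysis set. Read together, Sections 4.4, 9.5 and 10.1 let treated patients leave the ORR denominator on post-treatment facts, by decision of people not stated to be blind to response. This can bias the ORR and its interval, probably upward, and it undercuts the non-response rule in Section 7.4.4.

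The size is illustrative. The increases of 5.6 points (3 removed) and 12.5 points (6 removed) rest on 15 responders among 30 and on every removed case being a non-responder, so they are upper bounds for those numbers of removals. A fixed gain per removal should not be read from them: under the same assumption it runs from about 1.1 points each (9 responders, 3 removed: 3.3/3) to 2.5 points each (18 responders, 6 removed: 15.0/6).

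**What to change.** In Section 10.1, define the FAS as all enrolled subjects who received at least one dose of any study treatment. Delete from the definition both the qualifier on use according to protocol and the clause excluding removed cases. Delete the closing sentence that leaves treated excluded cases only in the SS.

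In Section 4.4, let the exclusions affect PPS membership only, under criteria fixed in advance, including a definition of an important eligibility violation. Align the Section 9.5 meeting with this, so that it settles PPS membership and does not alter the FAS.

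State in Section 10.3.1 that patients without an assessable response stay in the FAS as non-responders, as Section 7.4.4 already provides. The PPS then shows how sensitive the result is to the exclusions.

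The cost is wording only, with no added patients, visits or data. The reported ORR may be lower than under the current rule, and patients who start donafenib but never reach the combination would count in the denominator.

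### The per-protocol set keeps short-exposure patients who progress on a scan but drops those who die, which slightly flatters the supportive ORR, PFS and OS (minor)

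*Protocol*

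**What the plan says.** Section 10.1 sets up two efficacy populations: "Efficacy analysis will utilize both FAS and PPS, with FAS as the primary analysis set". The FAS is "all cases that have used the investigational drug at least once according to the protocol, excluding cases that have been removed". The PPS is a subset of the FAS. Its ordinary route of entry is to have "used the investigational drug according to the protocol for at least 2 weeks". There is one exception, for "Cases that have taken the drug for less than 2 weeks but have experienced radiologically confirmed disease progression within 12 weeks after starting the drug", provided the patient also meets the FAS criteria.

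The endpoint definitions settle how an early death counts once the patient is in a set. Section 7.4.4 states: "When the best overall response of subjects is 'unknown' or 'not assessed', it is considered as non-response when estimating ORR". Section 7.4.1 makes death from any cause a PFS event, and section 7.4.2 makes it the OS event.

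**The concern.** Below 2 weeks of drug, membership of the PPS depends on what happens to the patient afterwards. The authors saw that a bare exposure threshold would discard early failures and wrote an exception to recover them, but it recovers only failure seen on a scan. A patient who dies early, which is at least as clear a failure, stays out.

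The PPS is meant to show whether the FAS result holds among patients who were treated as planned. If early deaths are missing from it by definition, part of any advantage of the PPS over the FAS comes from the definition and not from adherence. What is at stake is the reading of a supportive analysis.

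**Working it through.** **Inputs**
- N = 30, from section 3.2: "This study is an exploratory study, using a fixed sample size of 30 cases". The protocol gives no expected response rate, no expected number of early deaths and no expected PPS size, so there is no figure of the plan's own to reproduce.
- x, the number of responders: an assumption. I use 18 of 30 and then show a range.
- k, the number of patients with under 2 weeks of drug who die without radiological progression: an assumption, shown for 1 to 3.
- For simplicity, all 30 patients are taken to be in the FAS and no other patient to leave the PPS.

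**Step 1: who is dropped.** Three patients each take drug for under 2 weeks.

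| Course | In FAS | In PPS | ORR if included |
|---|---|---|---|
| Radiological progression within 12 weeks, no response | yes | yes | non-response |
| Death, never scanned | yes | no | non-response (7.4.4) |
| Toxicity stop, no progression, scanned later | yes | no | whatever the scans show |

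The first two rows are both failures for ORR and both PFS events, yet only the first is kept.

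**Step 2: effect on ORR.** With all patients kept, ORR = x/N. With k deaths dropped, ORR = x/(N − k). The shift is xk/[N(N − k)]. Clopper-Pearson 95% intervals, the method named in section 10.3.1, for x = 18:
- k = 0: 18/30 = 60.0% (40.6 to 77.3)
- k = 1: 18/29 = 62.1% (42.3 to 79.3); shift 18 × 1/(30 × 29) = 2.1 points
- k = 2: 18/28 = 64.3% (44.1 to 81.4); shift 18 × 2/(30 × 28) = 4.3 points
- k = 3: 18/27 = 66.7% (46.0 to 83.5); shift 18 × 3/(30 × 27) = 6.7 points

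**Step 3: range over the assumed response count.** Shift in points for k = 1, 2, 3:
- 9/30 (30.0%): 1.0, 2.1, 3.3
- 15/30 (50.0%): 1.7, 3.6, 5.6
- 18/30 (60.0%): 2.1, 4.3, 6.7
- 24/30 (80.0%): 2.8, 5.7, 8.9

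**Step 4: effect on PFS and OS.** Take the k deaths as the earliest events, with no censoring before the median. With k = 2 and all 30 patients kept, the Kaplan-Meier curve has already fallen to 28/30 = 93.3% after those deaths, and it reaches 50% at the 15th event. With the two dropped, the curve is still at 100% at that time. It reaches 50% at the 14th of the remaining 28 events, which is the 16th in the full ordering. Both the early part of the curve and the median move in the favourable direction.

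**Step 5: toxicity withdrawals.** A dropped short-exposure patient may be a responder. With 18/30 as the reference, dropping two patients of whom one responded gives 17/28 = 60.7%, and dropping two responders gives 16/28 = 57.1%. The first is above 60.0% and the second below it, so the sign is open for this group.

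**The case against.** The main reply is that little depends on this. The FAS is primary, the study is exploratory and mainly descriptive, and the protocol sets no ORR threshold or decision rule. A minimum-exposure condition is also an ordinary feature of a supportive per-protocol set. All of that stands, and it limits the severity. It does not explain why the exception admits one early failure and omits another.

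The numbers dropped may also be very small. Patients enter with ECOG 0-1 and expected survival of at least 3 months, so the count could be zero. That is fair: k is an assumption, and the intervals above overlap heavily.

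A reader might infer four stronger points. The protocol does not support them.
- *The PPS ORR is biased upward in general.* Patients who stop drug are due CT/MRI at the end-of-treatment visit (4.3.3 and 6.4). If they have not progressed or started new antitumor therapy, they are then scanned every 12 weeks in the first 2 years (6.5.2). Under 7.4.4, a response confirmed before other antitumor therapy counts even after missed assessments. A short-exposure responder would be dropped while a short-exposure progressor is kept, which pulls the ORR down. The upward direction is certain only for patients who never respond, and early deaths without a scan are the clear case.
- *Everyone lost before the week-6 scan is removed.* The test is under 2 weeks of drug. A patient treated for 2 weeks according to the protocol who dies in week 4 stays in as a failure. Stopping one drug need not mean short exposure either, since section 5.3 allows the other drug to continue with HAIC.
- *No protocol deviation is a ground for exclusion.* Section 4.4 lists eligibility violations, non-compliance and concurrent antitumor therapy, and these reach the PPS through the FAS.
- *The primary ORR is affected.* This rule acts on the PPS only.

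**Conclusion.** The point holds in a narrow form and is minor. The exception in section 10.1 recovers radiological failures but not deaths among patients with under 2 weeks of drug. Each such death raises the supportive PPS ORR by about 2 points at N = 30 if 18 patients respond (1.0 to 2.8 points for one death across 9 to 24 responders). It also removes one of the earliest PFS and OS events.

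This rests on three assumptions: the number of responders, the number of such deaths, and that those who die had no response. The last follows from 7.4.4 when they were never scanned. The primary FAS analysis is not affected by this rule, and no direction can be claimed for toxicity withdrawals. Whether the PPS should keep every toxicity stop, or be rebuilt on a list of major deviations, is a matter on which statisticians differ and is not part of this point.

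**What to change.** In section 10.1, extend the PPS exception so that a patient with under 2 weeks of drug who dies from any cause within 12 weeks of starting drug is kept, on the same footing as one with radiologically confirmed progression in that period. State that an unassessed best response in these patients counts as non-response, as in 7.4.4, and that the death counts as the PFS and OS event under 7.4.1 and 7.4.2. Carry the same wording into the statistical analysis plan.

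The 2-week threshold and the FAS stay as they are, and no new data are needed. The cost is one clause and a PPS estimate that is slightly less favourable if any such deaths occur.
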